### Preoperative evaluation

2.6

#### Calibration of examiners

2.6.1

The calibration process of the 2 researchers who will perform the pre and postoperative evaluations will consist of joint training exercises performed 3 times in 1 volunteer who will not be part of the experimental groups. The data will be discussed among these researchers to achieve an excellent level of agreement. Subsequently, each examiner will individually carry out the measures proposed in the study in 10 adult volunteers who will not be included in the sample, and the data obtained will be submitted to the intraclass correlation coefficient test. Once the agreement between the examiners is evaluated as excellent, the measurements will be performed on the sample participants.

#### Edema evaluation

2.6.2

Using a flexible plastic millimeter tape (0.5 mm accuracy), 5 facial measurements will be taken, corresponding to the distances between the points listed below^[14]^

Line A – posterior tragus point to the most lateral point of the labial commissure;Line B – tragus posterior point to pogonium;Line C – tragus posterior point to the lateral corner of the eye;Line D – lateral corner of eye to lowest point of jaw angle;Line E – lower point of the angle of the mandible (gonio) to the middle of the nasal bone.

The measurements will be taken by 2 of the previously calibrated researchers. The values of the 5 measures (A, B, C, D, E) will be summed to obtain the data of each participant.

#### Extra and intraoral sensitivity tests

2.6.3

The evaluation of extra and intraoral sensitivity will be performed in 6 regions: below the lower eyelid, cheek, nose wing, upper lip, oral buccal mucosa, and oral palatal mucosa on both sides. The tests will be performed sequentially, with a 2 to 3 minutes interval between each. The participant will receive instructions on the tests that will be initially performed on the back of his hand so he can become familiar. The test room will be prepared to provide a calm environment where the participant will be semi-seated and with eyes closed.^[13]^

#### Evaluation of the sensation of light touch

2.6.4

For this evaluation, 20 mm fragments of 3-0, 4-0, 5-0, and 6-0 diameter mononylon suture threads (Ethicon; Johnson & Johnson, Cincinnati, OH) will be used. They will be fixed perpendicularly in a stainless steel holder of 10 cm in length. The participants’ response to the test will be classified (from 0 to 4 points) based on Table 1.^[13,16]^ In the case of lack of sensitivity, no points will be awarded, and a maximum of 4 points will be awarded for each side in each participant. The light touch sensation aims to evaluate the existence of an axonal neuropathy because it evaluates myelinated fibers type A alpha.^[13,16]^

**Table 1 T1:**
[figure not shown]
Attribution of points for positive response to the light touch test.

#### Stinging sensation

2.6.5

This test will be performed using a very smoothly applied carpule syringe needle in the same areas described earlier on both sides of each participant. The determined response will be the perception of the touch of the needle, being recorded only as positive or negative, punctuating as: positive (1) and negative (0). This test aims to evaluate myelinated fibers type delta A and type C.^[13,16]^

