### Global sensitivity index

3.3

The sensitivity tests described above will be repeated in all participants, on both sides on postoperative days 7, 30, 60, 90, and 120. The results of the light touch and sting sensation tests will be added (maximum value 5 points/side/participant/period) and this value will be called qualitative sensitivity. On the other hand, the measurements obtained in the static 2-point discrimination test (item 2.6.5) and dynamic 2-point discrimination test (item 2.6.6) in each experimental period will be subtracted from those obtained in the respective tests in the preoperative evaluation and the value of the difference between these measures will be classified according to Table 4. The value of the sum of the classifications obtained in the static 2-point discrimination test (item 2.6.5) and dynamic 2-point discrimination test (item 2.6.6) in each experimental period will be denominated quantitative sensitivity (summing 0–10 points/side/participant/period).^[13,16]^

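### The stinging test is aimed at A-delta and C fibres, but its written rule scores any felt touch of the needle as positive, so isolated loss of sharp sensation does not show in the sensitivity index

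*Protocol article*

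**What the plan says.** Section 2.6.5 of the protocol article is headed as a test of stinging. It describes the stimulus: "This test will be performed using a very smoothly applied carpule syringe needle in the same areas described earlier". It then defines the result: "The determined response will be the perception of the touch of the needle, being recorded only as positive or negative", with 1 point for positive and 0 for negative. It closes with the purpose: "This test aims to evaluate myelinated fibers type delta A and type C".

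The light-touch test in section 2.6.4 uses suture threads of four diameters. It is scored from 0 to 4 ("a maximum of 4 points will be awarded for each side in each participant") and is assigned to a different fibre type: "it evaluates myelinated fibers type A alpha".

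Section 3.3 combines the two: "The results of the light touch and sting sensation tests will be added". The sum, at most 5 per side, is called qualitative sensitivity. It is added to a quantitative part of 0 to 10 from the two 2-point discrimination tests, giving a GSI of at most 15 per side. The GSI is then put into classes by Table 5, which is not shown.

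The Outcome measures section lists paresthesia among the primary outcomes, at 7, 30, 60, 90 and 120 days. Section 3.3 repeats the sensitivity tests on those same days, and the article describes no other measure of paresthesia.

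**The concern.** The heading and the stated aim name one sensation, and the scoring rule records another. A-delta and C fibres are associated with sharp and painful sensation. That is general physiology and is not spelled out in the article, although the word stinging in the heading points the same way. The rule asks only whether the participant notices the needle's touch. It does not ask whether the needle feels sharp, and it does not ask the participant to tell sharp from blunt.

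If the examiners follow the rule as written, the one item meant to reflect A-delta and C function gives no information specific to it. A participant who still feels contact in the infraorbital area but no longer feels sharpness is recorded as normal on this item. Recovery of sharpness in such a participant would also go unrecorded. Because the item feeds the index behind a primary outcome, a difference between arms confined to that sensation would not be visible.

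**Working it through.** **1. Which test covers which fibres.** Sections 2.6.4 to 2.6.7 assign the four tests as follows.

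| Test | Stated target | Response scored |
|---|---|---|
| Light touch (2.6.4) | A-alpha | touch of graded threads, 0 to 4 |
| Stinging (2.6.5) | A-delta and C | touch of the needle, 0 or 1 |
| Static 2-point (2.6.6) | slow-adapting A-beta | shortest distance felt as two tips |
| Dynamic 2-point (2.6.7) | fast-adapting A-beta | shortest distance felt as two tips |

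Only the stinging test is directed at A-delta and C fibres. No other section gives a sharpness or pain criterion for the needle.

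**2. Reproducing the index totals.** These use the per-side maxima in sections 2.6.4, 2.6.5 and 3.3.

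- Qualitative maximum = light touch + sting = 4 + 1 = 5, as stated.
- GSI maximum = qualitative + quantitative = 5 + 10 = 15, as stated.

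**3. Weight of the item.**

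- Share of qualitative points: 1 / 5 = 20%.
- Share of the GSI: 1 / 15 = 6.7%.
- Share of the points aimed at A-delta and C fibres: 1 / 1 = 100%.

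**4. What the item records under each rule.**

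| State of the side | Rule as written | Rule scoring sharpness |
|---|---|---|
| contact felt, sharpness felt | 1 | 1 |
| contact felt, sharpness lost | 1 | 0 |
| contact not felt | 0 | 0 |

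The two rules differ only in the middle row.

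**5. Illustrative side in the middle row, with all other tests normal.**

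- Rule as written: 4 + 1 + 10 = 15, identical to an intact side.
- Rule scoring sharpness: 4 + 0 + 10 = 14.
- Difference: 15 - 14 = 1 point, the largest direct effect possible for one side at one assessment.

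Two things cannot be calculated. The documents do not say how often sharpness is lost with contact preserved after this operation. Without the Table 5 cut-offs, it is also unknown whether one point would move a side to another class. The sample size does not enter the argument.

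**The case against.** The strongest reply is that this is loose English for an ordinary pinprick test. The heading, the aim and section 3.3 all speak of stinging, and section 2.6.3 has participants instructed and familiarised on the back of the hand. That may well be what was intended. But the explicit response rule says touch, nothing shown corrects it, and two examiners must apply it in the same way before surgery and at five later assessments. If pinprick was meant, stating it costs nothing.

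A second reply is that the article condenses a fuller protocol and credits the test to cited sources, neither of which is available here. This would answer a complaint about missing detail. It does not answer a criterion that the article states and that conflicts with its own aim. It does stand as a caution about the fix: if the cited index scores needle perception, changing one item could put the index out of step with the Table 5 classes.

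A reader might also infer more than the text supports:

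- **That the stinging test repeats the light-touch test.** It does not. The stimulus and the scale differ: one needle scored 0 or 1, against four threads scored 0 to 4. The overlap lies only in the kind of response accepted.
- **That touch loss is generally counted twice.** A participant who misses only the finest thread can still feel the needle. Both items fall together only when needle contact is not felt at all.
- **That no pain-fibre loss can reach the index.** Loss severe enough that the needle is not felt still scores 0. Only loss of sharpness with contact preserved is hidden.
- **That the rule biases the comparison.** It is the same in both arms, and section 2.8 keeps participants and examiners unaware of allocation.

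**Conclusion.** The point holds in a limited form. The response rule in section 2.6.5 conflicts with the aim stated in the same section. Taken literally, it leaves isolated loss or recovery of sharp sensation out of the GSI. The direct effect is at most 1 of 15 points per side at each assessment (1 of the 5 qualitative points), and it is a loss of sensitivity, not a bias between arms. No figure can be put on the share of participants affected, on the GSI class, or on the paresthesia comparison.

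This rests on three assumptions: that examiners would apply the rule as worded, that A-delta and C function is meant to show as sharp or stinging sensation, and that the GSI is the measure of the primary paresthesia outcome, as the matching assessment days indicate. If examiners already score sharpness in practice, what remains is a wording error that still needs correcting.

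**What to change.** Reconcile the response rule in section 2.6.5 with its stated aim. Suggested wording: the item is positive (1) only if the participant, with eyes closed, reports the needle as sharp or stinging; it is negative (0) if the needle is felt as blunt touch only or is not felt. Apply the same rule before surgery and at 7, 30, 60, 90 and 120 days, and include it in the examiner calibration and in the familiarisation that section 2.6.3 already provides.

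The cost is one sentence in the protocol and one line in examiner training. The needle, sites, visits and maxima of 5 and 15 stay as they are. There are two downsides. A sharp-or-blunt answer is slightly more subjective than reporting contact. The sponsor should also check that the revised rule still agrees with the cited index and with the Table 5 classes.

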#### Static 2-point discrimination test

2.6.6

To perform this test, the same apparatus suggested by Gulses et al,^[13]^ aimed at evaluating the slow-adapting A beta myelinated fibers, will be made. Thus, a Biotone Dentsply color scale (Dentsply Sirona Brazil, São Paulo, Brazil) with 10 acrylic teeth will be used. Each tooth will receive, on the side face, 2 parallel holes separated by distances of 1 to 10 mm. Afterward, 0.8 mm stainless steel wires with a blunt tip will be inserted into these holes and fixed with acrylic resin. The crowns of the teeth will be marked with numbers that will identify the distance between the points. The test will be performed by applying the pair of tips very gently in the same areas described previously on both sides of each participant. Each pair of tips will be tested at once, starting with a random numbering. Then, the examiners will increase or decrease the space between the wires, testing the doubles of greater or lesser numbers as indicated by the initial response. The shortest distance in which the participant feels 2 tips will be considered.

#### Dynamic 2-point discrimination test

2.6.7

Using the same device from the static test, now aiming to evaluate fast-adapting A beta myelinated fibers, a randomly chosen pair of tips will be moved from proximal to distal (within 1–2 cm), in the same anatomical regions as previously indicated, with as little pressure as possible. The participant will be asked to respond if they feel 1 or 2 tips. The numbering of the first pair of points will be chosen at random and then the order of use of the subsequent ones will be followed by increasing or decreasing their values. The shortest distance in which the participant feels 2 tips will be considered.

#### Radiographic examination of the anterior region of the palatine suture

2.6.8

The optical density (OD) of the alveolar bone in the anterior region of the palatine suture will be the basis for evaluating bone repair after surgery.^[12]^ A periapical radiograph (of the upper incisors region with the radiographic technique of parallelism) of each participant using a 70 kVp RX transmitter will be obtained (Dabi Atlante Indústria Médico Odontológica LTDA, São Paulo, Brazil, Spectro 70X Selectronic). To standardize the radiographic shots in the different experimental periods, the focal length will be 30 cm and the exposure time will be 0.05 seconds. Five radiographic shots will be performed in different time frames, with all applicable biosafety system with individual protectors and lead apron. The intraoral positioner will be inserted with resistant molding material, silicone condensation (Optosil Xantopren – Heraeus Kulzer, Brazil, São Paulo), to obtain the impression of the edges of the lower incisor teeth that will guide the positioner in future shots. The radiographic films will be revealed in the same processor. The images will then be digitized and analyzed with the help of Image J software (National Institute of Health [NIH], Bethesda, Maryland).

To do this, an area in the anterior region between the upper central incisors will be selected for reading and counting the number of pixels of the scanned radiographic images. To obtain the delimitation of this area, the procedure described by Angeletti et al^[12]^ will be used. Initially, a straight line will be drawn on the alveolar bone crest between the crowns of the upper central incisors, which will be designated as the minor base (*b*). From this line, 2 lines (*h*) will be drawn parallel to the long axis of the right and left upper central incisors with a length of 15 mm. To join the lines h, another line will be drawn parallel to the smaller base which will be called the larger base (*B*), thus forming a trapezoid. The area and the number of pixels of each trapezoid will be recorded by the same professional in 3 different times with an interval of 15 days between each measurement. Then, the searcher will access the area values and number of acquired pixels and will calculate the average of these values. The trapezoidal area of each image will be calculated by the following formula: 

The OD in the region of the anterior palatine suture of each participant will be obtained by dividing the number of pixels by the trapezoid area.

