## Outcome measures

3

All variables will be evaluated by the same 2 examiners, before and after surgery for periods of 1 to 120 days according to each variable. The primary outcomes of the study are: the occurrence and intensity of pain and edema (with evaluation periods of 1, 2, 7, and 14 days after surgery), the occurrence of paresthesia (with evaluation periods of 7, 30, 60, 90, and 120 days after surgery) and bone repair in the anterior palatine suture region (with evaluation periods of 30, 60, 90, and 120 days after surgery). The secondary outcomes of the study are: headache, otalgia, nausea, hematoma, nasolacrimation, nasal bleeding, and surface temperature (with evaluation periods of 1, 2, 7, and 14 days after surgery), dysphagia (with evaluation periods of 7 and 30 days after surgery), anxiety (7 days after surgery), quality of life (with periods of evaluations of 7 and 30 days after surgery), and use of analgesics and anti-inflammatory drugs on the 14th day. Information on gender (male/female), race, age (in years), and educational background (from illiterate to full graduate) will also be collected.^[22,23]^

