### Bone repair evaluation

3.4

Periapical radiographs will be obtained from each participant, as described previously, after 30, 60, 90, and 120 days of surgeries. The OD of the alveolar bone in the anterior region of the palatine suture, in each experimental period, will be calculated and compared with that obtained in the preoperative radiographic examination. Images will be scanned and analyzed with Image J software (NIH).

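### The optical density formula for bone repair, a primary outcome, divides a pixel count by an area and so, as written, carries no information on bone density

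*Protocol article*

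**What the plan says.** Section 3 (Outcome measures) of the protocol article makes bone repair a primary outcome, assessed at days 30, 60, 90 and 120. Section 2.6.8 states that the optical density (OD) of the alveolar bone "will be the basis for evaluating bone repair after surgery".

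Three statements in 2.6.8 define OD, and they agree with one another:

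- An area between the upper central incisors "will be selected for reading and counting the number of pixels of the scanned radiographic images".
- What is recorded from each image is a count and an area: "The area and the number of pixels of each trapezoid will be recorded by the same professional in 3 different times". The three readings are then averaged.
- OD "will be obtained by dividing the number of pixels by the trapezoid area".

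The region is a trapezoid whose two sides follow the long axes of the incisors "with a length of 15 mm". Section 3.4 (Bone repair evaluation) adds that the OD at each visit "will be calculated and compared with that obtained in the preoperative radiographic examination".

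The article nowhere mentions grey level, pixel intensity, integrated density, or a threshold that would restrict the count to some of the pixels.

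**The concern.** On a scanned film, mineralisation shows as grey level. It does not change how many pixels lie inside a drawn outline, which depends only on the size of the outline and the fineness of the scan. Dividing the count by the area removes the size and leaves the fineness of the scan.

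A reader who followed 2.6.8 to the letter would therefore obtain essentially the same number for unmineralised and for fully repaired bone. The comparison between arms and the comparison with the preoperative film would reflect only rounding, scaling, scan settings or tooth geometry. Section 2.6.8 plans five radiographs per participant. With 72 participants (section 2.4) that is up to 5 × 72 = 360 exposures taken for this measure.

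**Working it through.** The protocol gives no numerical value for OD, so there is no figure to reproduce. The check is of the formula itself.

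**Inputs from the protocol (2.6.8).** The numerator is the pixel count of the trapezoid, the denominator is the trapezoid area, and the sides are 15 mm long.

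**Assumptions, for illustration only.** Scan resolutions of 300, 600 and 1200 dpi; mean grey levels of 60, 120 and 180; trapezoid bases b/B of 2/6, 6/10 and 3/12 mm. The protocol states none of these.

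**Step 1: the quotient as written.** A region of A mm² scanned at r pixels/mm contains about N = r²A pixels. Hence N/A = r² = (dpi/25.4)². If the area is itself measured in pixels, the quotient is 1.

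| Assumed dpi | (dpi/25.4)² | N/A on simulated trapezoids |
|---|---|---|
| 300 | 139.5 | 139.1 to 139.7 |
| 600 | 558.0 | 557.8 to 558.2 |
| 1200 | 2232.0 | 2231 to 2233 |

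For a given shape and resolution, N/A was identical at all three grey levels. The small spread in the last column is pixel rounding at the edges of the different shapes.

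**Step 2: geometry.** The area formula was not available in the text I worked from, and I do not count that against the plan. If it takes the 15 mm slanted side as the height, the area is too large and N/A falls by the cosine of the side's tilt.

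- Bases 6/10 or 2/6 mm: half-difference 2 mm, true height √(15² − 2²) = 14.87 mm, ratio 14.87/15 = 0.991, so 558 becomes about 553.
- Bases 3/12 mm: half-difference 4.5 mm, true height √(15² − 4.5²) = 14.31 mm, ratio 0.954, so 558 becomes about 532.

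The quotient can therefore vary between films, but with incisor angulation and not with bone.

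**Step 3: the same regions with a grey-level numerator, at 600 dpi.**

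| Mean grey level | Pixel count / area | Sum of grey values / area | Sum of grey values / pixel count |
|---|---|---|---|
| 60 | about 558 | about 33,450 | 60 |
| 120 | about 558 | about 66,950 | 120 |
| 180 | about 558 | about 100,450 | 180 |

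Both grey-level versions follow the image; the pixel count does not. Dividing by the pixel count also removes r² from the result, which dividing by area does not.

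**The case against.** The strongest reply is that the literal reading was not intended. The measure is called optical density, which is a grey-level quantity, and the phrase about counting pixels may be a loose rendering of a pixel-value output or of a count above a threshold. The Discussion reports that the earlier laser study after the same surgery, which 2.6.8 cites as its basis for OD, found better bone regeneration with photobiomodulation in all periods. A measure that returned only scan resolution could hardly have shown that.

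As an account of intent this is plausible, and I accept it as probable. It does not settle the definition. The text specifies a count three times, it records the pixels of the whole trapezoid, and it invokes the cited study's procedure only for outlining the area before giving its own OD formula. A sum of grey values, a mean grey value and a thresholded count are different endpoints. Leaving the choice until images are read would leave a primary outcome open to definition after the fact.

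A second reply is that a journal article leaves software settings to the full protocol. That is fair for scan resolution, calibration and the like. Here, however, the formula is stated, and it is the stated formula that fails.

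Four stronger inferences are tempting, and the document does not support them:

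- *The quotient is the same for every participant and visit.* Not strictly: scaling, or the choice of height in step 2, can move it.
- *Power for this outcome equals the 5% error rate.* That would need residual noise with the same distribution in both arms. With a true constant the test is degenerate. No power figure should be attached.
- *The trial cannot answer its bone repair question.* Only if the formula is applied literally. The films can be re-read, and the other three primary outcomes are unaffected.
- *The lack of a density reference on the same film is an error.* It is a design preference. Section 2.6.8 already fixes tube voltage, focal length, exposure time, paralleling technique, an impression-guided positioner and the processor.

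**Conclusion.** The point holds for the formula as written. OD in 2.6.8, carried into 3.4, is pixels per unit area. It reflects scan resolution and possibly a geometric factor, and contains no information on bone density. Used literally, it cannot show a treatment effect on bone repair or a change from the preoperative value.

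The conclusion needs no assumption beyond a digitised image with a fixed pixel grid. The dpi values, grey levels and trapezoid shapes only illustrate it. What remains uncertain is whether the trial's readers would apply the formula literally. The wording probably stands for a grey-level measure, in which case the defect lies in the text and not in the practice. It still has to be corrected before analysis, because this is the only definition the article gives for a primary outcome.

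**What to change.** In 2.6.8 and 3.4, before any images are analysed:

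1. Replace the pixel-count numerator with the sum of pixel grey values in the trapezoid, and divide by the trapezoid's pixel count, so that the measure is the mean grey value.
2. Read it from the same films in the same software, with scan settings held fixed for all participants and visits.
3. Average the three readings already planned, and compare that average with the preoperative one as 3.4 intends.
4. Call the result mean grey value unless a conversion to optical density is specified, since the two are not the same without calibration.

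An optional refinement is to normalise to a region on the same film whose density should not change.

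The cost is a wording change and a different output column from the image software. There are no further exposures, and the radiographs and reader stay the same. Section 2.4 bases the sample size on variability in three cited articles but gives no effect size or standard deviation, so its authors should confirm that the bone repair variability they used refers to the measure now defined.
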